## Abstract

**Background:**

Visual confirmation of a suspicious lesion in the urinary tract is a major corner stone in diagnosing urothelial carcinoma. However, during cystoscopy (for bladder tumors) and ureterorenoscopy (for tumors of the upper urinary tract) no real-time histopathologic information can be obtained. Confocal laser endomicroscopy (CLE) is an optical imaging technique that allows for in vivo high-resolution imaging and may allow real-time tumor grading of urothelial lesions.

**Objective:**

The primary objective of both studies is to develop descriptive criteria for in vivo CLE images of urothelial carcinoma (low-grade, high-grade, carcinoma in situ) and normal urothelium by comparing CLE images with corresponding histopathology.

**Methods:**

In these two prospective clinical trials, CLE imaging will be performed of suspicious lesions and normal tissue in the urinary tract during surgery, prior to resection or biopsy. In the bladder study, CLE will be performed in 60 patients using the Cystoflex UHD-R probe. In the upper urinary tract study, CLE will be performed in 25 patients during ureterorenoscopy, who will undergo radical treatment (nephroureterectomy or segmental ureter resection) thereafter. All CLE images will be analyzed frame by frame by three independent, blinded observers. Histopathology and CLE-based diagnosis of the lesions will be evaluated. Both studies comply with the IDEAL stage 2b recommendations.

**Results:**

Presently, recruitment of patients is ongoing in both studies. Results and outcomes are expected in 2018.

**Conclusions:**

For development of CLE-based diagnosis of urothelial carcinoma in the bladder and the upper urinary tract, a structured conduct of research is required. This study will provide more insight in tissue-specific CLE criteria for real-time tumor grading of urothelial carcinoma.

**Trial Registration:**

Confocal Laser Endomicroscopy: ClinicalTrials.gov NCT03013894; https://clinicaltrials.gov /ct2/show/NCT03013894?term=NCT03013894&rank=1 (Archived by WebCite at http://www.webcitation.org/6wiPZ378I); and Dutch Central Committee on Research Involving Human Subjects NL55537.018.15; https://www.toetsingonline.nl /to/ccmo_search.nsf/fABRpop?readform&unids=6B72AE6EB0FC3C2FC125821F001B45C6 (Archived by WebCite at http://www.webcitation.org/6wwJQvqWh). Confocal Laser Endomicroscopy in the upper urinary tract: ClinicalTrials.gov NCT03013920; https://clinicaltrials.gov/ct2/show/NCT03013920? term=NCT03013920&rank=1 (Archived by WebCite at http://www.webcitation.org/6wiPkjyt0); and Dutch Central Committee on Research Involving Human Subjects NL52989.018.16; https://www.toetsingonline.nl/to/ccmo_search.nsf/fABRpop?readform&unids=D27C9C3E5755CFECC12581690016779F (Archived by WebCite at http://www.webcitation.org/6wvy8R44C).

## Introduction

Urothelial carcinoma is the most common malignancy of the urinary tract. The majority of these tumors are located in the bladder and only 5% are located in the upper urinary tract [1]. For bladder cancer, direct visualization of the urothelium with white light cystoscopy (WLC) is the cornerstone for diagnosis and follow-up. Despite its effectiveness and established role, WLC has limitations, such as, its diagnostic accuracy, especially for carcinoma in situ (CIS) [2]. Histopathologic grading and staging of urothelial carcinoma are essential for diagnosis, prognosis and choice of therapy. However, real-time histopathologic assessment is lacking during cystoscopy in an outpatient setting as well as in the operating theatre. For upper tract urothelial carcinoma (UTUC), ureterorenoscopy (URS) with endoscopic biopsies of suspicious areas is considered the diagnostic standard. Also for UTUC, histopathologic evaluation is essential for prognosis and treatment selection as endoscopic treatment is reserved for low grade tumors only [3]. Similar to the diagnostics of bladder cancer, real-time histopathologic assessment is lacking during URS. The use of optical imaging techniques, such as Confocal Laser Endomicroscopy (CLE), may enable real-time optical biopsies to overcome these limitations for bladder cancer and UTUC evaluation.

CLE is a fiber optic probe–based imaging technique that enables real-time in vivo optical sectioning of tissue. The Cellvizio CLE system uses a low-energy 488 nm laser source. The presence of a pinhole limits the detection to in-focus backscattered fluorescent light, enabling high resolution imaging in a single horizontal plane. CLE imaging requires the administration of a fluorescent contrast agent. The most commonly used fluorescent dye is fluorescein. Topical or intravenous application of fluorescein stains the extracellular matrix and enables visualization of the cellular microarchitecture and morphology. Tissue types can be differentiated based on these specific cellular features. For in vivo endoscopic CLE imaging, various sized probes with different image properties are commercially available. CLE was initially applied for in vivo imaging in the gastrointestinal tract and applications in pulmonology are explored [4-6]. In urology, CLE was first examined in the bladder. It seemed feasible to differentiate between normal mucosa and urothelial carcinoma using CLE imaging in a pilot study. Based on histopathology from resected bladder tumors, CLE criteria to differentiate between normal bladder tissue, low-grade, and high-grade bladder tumors were proposed.[7,8] These criteria have also been suggested for the upper urinary tract as the histologic morphology and microarchitecture are alike. However, a CLE probe with different imaging properties is used in the upper urinary tract and only small patient cohorts have been evaluated [9,10].

The development of CLE towards real-time optical biopsies of urothelial carcinoma may lead to advances in diagnosis and prognosis and may affect the cost-benefit of the disease management. Currently, bladder cancer is the most expensive solid malignancy per patient. The high recurrence rate of early stage tumors with long-term survival and adjuvant treatments with close follow-up results in high costs [11,12]. Even though laser fulguration of low-risk tumors has been performed in outpatient settings, it is not widely used due to the lack of histologic confirmation and, therewith, the risk of inadequate treatment [13,14]. Immediate evaluation of tumor grade with CLE could potentially increase the application of laser fulguration and enable treatment of real-time confirmed low-grade tumors in an outpatient setting. Application of laser fulguration in an outpatient setting would lead to an increase in availability of treatment of low-grade bladder cancer and reduction of medical costs. Potentially, CLE may also allow for real-time evaluation of surgical radicality and, therewith, reduce recurrence rates in urothelial cancer. In the upper urinary tract, CLE has the potential to improve the diagnostic approach for UTUC.

Accurate staging and grading of UTUC remains challenging. Visual white light assessment of UTUC grade during URS is inaccurate in approximately 30% of the cases [15]. Moreover, the restricted anatomic space of the upper urinary tract and the subsequent miniaturization of tissue-harvesting instruments limit the yield of ureteroscopic biopsies. The diagnostic yield and the diagnostic accuracy for tumor stage of endoscopic biopsies are limited [16,17]. However, tumor grade from endoscopic biopsies may indicate tumor stage [18,19]. As such, tumor grade from endoscopic biopsies is a major decisive factor for endoscopic treatment eligibility. Though, in 69-90% of endoscopic biopsies, tumor grade is in concordance with the histopathologic grade from radical resection [17,18,20,21]. Moreover, endoscopic biopsies hold a risk of complications.

CLE may overcome such diagnostic limitations for tumor grade assessment. Optical real-time assessment of tissue type and tumor grade could aid perioperative clinical decision-making. Histologic assessment without tissue biopsies could prevent possible impaired endoscopic vision after biopsies during URS. Additionally, the digital data from CLE imaging allows for real-time computer aided diagnosis with software, augmenting the practical and diagnostic value of optical imaging techniques. Further exploration of different optical imaging modalities for tumor diagnosis may lead to multimodal optical biopsies for real-time tumor grading and staging, possibly replacing tissue biopsies in future. However, a structured conduct of research is required to guide us towards optical biopsies. The aim of these two study protocols is to contribute to the development of essential knowledge for CLE-based diagnosis of urothelial carcinoma in the bladder and the upper urinary tract. In this paper, we describe two study protocols for CLE in the urinary tract together as both protocols share many methodological and disease-specific similarities.

## Methods

### Study Objectives

The primary objective of both studies is to develop descriptive criteria for in vivo CLE images of urothelial carcinoma (low-grade, high-grade, CIS) and normal urothelium by comparing CLE images with corresponding histopathology.

Secondary objectives are to develop a CLE image atlas of the urinary tract, to assess the technical feasibility and procedure-related adverse events, to assess CLE image quality, to qualitatively evaluate CLE images, to preliminarily assess the diagnostic yield, and to establish an estimation of the diagnostic accuracy of CLE-based diagnosis in comparison with histopathology and to assess inter-observer agreement.

### Study Design

Approval of the local medical ethical committee was obtained for both study protocols (registry number: NL55537.018.15 and NL52989.018.16). Both studies are prospective, single-centre, in vivo, observational human studies to assess CLE features of normal urothelium and urothelial carcinoma (low-grade, high-grade or CIS) in the bladder and in the upper urinary tract. Both explorative studies are in agreement with the IDEAL stage 2b recommendations [22]. The two study protocols differ mainly in the location of urothelial carcinoma, and subsequently, the surgical approach, the type of CLE probe, the administration of fluorescein, and the reference standard. Differences in protocols are explained separately and listed in Table 1.

For both studies, CLE images are recorded with a fiber optic probe–based system (Cellvizio 100 series, Mauna Kea Technologies, Paris, France). The Cystoflex UHD-R probe of 8.4 Fr (Mauna Kea Technologies, Paris, France) is used for CLE imaging in the bladder. The Uroflex-B probe of 2.7 Fr (Mauna Kea Technologies, Paris, France) is used in the upper urinary tract. The smaller Uroflex-B probe contains less optical fibers and, therewith, a lower image resolution compared to the Cystoflex UHD-R probe. Both forward-looking probes are illustrated in Table 1 and Figure 1.

CLE imaging requires the application of a fluorescent contrast agent. Fluorescein (fluoresceinedisodium, Fresenius Kabi, Zeist, The Netherlands) is a non-toxic and commonly used fluorescent dye for CLE imaging [23]. It stains the extracellular matrix and is administered topically prior to CLE imaging during the surgical procedure.

In both studies, patients will undergo in-vivo CLE imaging during surgery, prior to resection or biopsy of suspicious areas for standard histopathologic assessment. The probes are introduced through the working channel of the standard endoscopes. In the bladder, a Karl Storz cystoscope of 22 Fr with 0° optics is used for CLE imaging. Transurethral resection is subsequently performed with a Karl Storz or Olympus resectoscope of 26 Fr. For CLE imaging of the upper urinary tract, a flexible digital ureterorenoscope of 8.5 Fr is used (Karl Storz Flex Xc or Olympus V2). After placing the probe in direct contact with the region of interest, image sequences of 8–12 frames per second of the real-time visualization of the cellular microarchitecture are recorded (Multimedia Appendices 1 and 2). In general, recording is conducted in both protocols twice for 1 minute of the region of interest. In case of multiple regions of interest, multiple CLE recordings are performed. At a later stage, recorded CLE images will be analyzed independently by three blinded observers and compared to the corresponding histopathology. For CLE imaging in the bladder, the reference standard for comparison of histopathology will be the specimen of the en-bloc resected lesion. For the upper urinary tract, the reference standard will be the specimen of the radical resection (radical nephroureterectomy [RNU] or segmental ureter resection [SU]). Histopathology analysis is performed according to the standard clinical protocol and is performed by a specialized uropathologist ([name]), who is blinded for the CLE images. A follow-up of 30 days is considered to register any adverse events following the study procedure.

### Population and Sample Size

Patients eligible for either study are >18 years with a suspicious lesion in the urinary tract, scheduled for either transurethral resection (TURB) (lower urinary tract) or diagnostic URS (upper urinary tract). The main exclusion criteria are fluorescein allergy and pregnancy (Table 1). All patients will be recruited in the AMC Hospital (Amsterdam, The Netherlands), and all study procedures will be performed in this institution. Patients will be informed about the study in oral and written form. Patient inclusion is confirmed by signing written informed consent. Patients will only be included in one study at the time. A total of 60 consecutive evaluable patients with bladder tumors or suspicion of CIS will be included in the bladder cancer study. Based on prevalence, we expect to include 32 low-grade, 22 high-grade, and 6 CIS lesions. For the upper urinary tract study, 25 patients with UTUC that will undergo a radical treatment after the diagnostic URS will be included. However, the indication for radical treatment is determined after diagnostic URS. In general, about one-third of the UTUC patients are treated with radical surgery in our centre. Therefore, we expect to include 70 consecutive UTUC patients to reach the total number of 25 patients who will undergo radical treatment. Considering the possible selection bias for radical treatment, we expect to include 10 low-grade, 12 high-grade, and 3 CIS lesions. These sample sizes are based on prior publications and comply with the IDEAL recommendations for explorative studies [7,9,22].

**Table 1 table1:** Differences between the two study protocols. CIS: carcinoma in situ; CLE: Confocal Laser Endomicroscopy; RNU: radical nephroureterectomy; SU: segmental ureter resection, TURB: transurethral resection bladder tumor; URS: ureterorenoscope; UTUC: upper tract urothelial carcinoma.

Variables	CLE bladder study	CLE upper urinary tract study
Population	60 consecutive patients with primary or recurrent bladder tumor	25 patients with UTUC that will undergo a RNU or SU after diagnostic URS with CLE imaging
Inclusion criteria	bladder tumor or possible CIS scheduled for TURB signed informed consent	suspicion of UTUC scheduled for diagnostic URS signed informed consent
Exclusion criteria	allergy for fluorescein possible pregnancy or lactating women	allergy for fluorescein possible pregnancy or lactating women Patients not eligible for RNU
Urologic instruments at use	Karl Storz 22 Fr cystoscope with 0° optics for CLE imaging, and Karl Storz or Olympus 26 Fr resectoscope for transurethral resection	Karl Storz Flex Xc or Olympus V2 8.5 Fr flexible digital ureterorenoscope
Contrast agent	Topical application of 300-400 mL of 0.1% fluorescein via Foley catheter and left indwelling for 5 minutes	Topical application of 0.5 mL 2.5% fluorescein via working channel for immediate imaging
CLE probe	Cystoflex UHD-R diameter 2.6 mm lateral resolution 1 µm field of view 240 µm imaging depth 50-65 µm	Uroflex-B diameter 0.85 mm lateral resolution 3.5 µm field of view 320 µm imaging depth 40-70 µm
Histopathologic reference standard	En-bloc resected bladder tumor	RNU or SU

**Figure 1 figure1:**
[figure not shown]
Cellvizio CLE (Confocal laser endomicroscopy) system and the probes used for the urinary tract. (A) Cellvizio CLE system; (B) The two different probes used in the urinary tract. On the left the Cystoflex UHD-R probe with a diameter of 2.6 mm, which is used in the bladder. On the right the Uroflex-B probe with a diameter of 0.85 mm, which is used in the upper urinary tract; (C) RAW image of the Cystoflex UHD-R probe displaying the single fibers; (D) RAW image of the Uroflex-B probe displaying the single fibers.

### Study procedures

#### Protocol for Confocal Laser Endomicroscopy in the Bladder

In the operating theatre prior to the TURB under general or regional anaesthesia, visual inspection with WLC and image enhancement modalities (narrow band imaging or Image1S) will be performed. At least one suspicious lesion (papillary or flat) and one region of normal appearing bladder tissue will be selected for CLE imaging. The regions of interest will be marked laterally with the cautery electrode for topographic matching. After marking the regions of interest, 300-400 mL of fluorescein (0.1% fluorescein diluted in saline) will be administered intravesically using an indwelling catheter. After instillation of the fluorescein for 5 minutes, the bladder will then be emptied and excessive fluorescein will be rinsed out. The Cystoflex UHD-R probe will be introduced through the working channel of a 22 Fr Karl Storz cystoscope with 0° optics. After placing the probe into direct contact and perpendicular to the tissue, CLE images will be recorded twice for approximately 1 minute of each marked region. After CLE imaging, the tumor will be resected en-bloc and a small chip of the marked normal urothelium will be resected for histopathologic matching. Transurethral resection is performed with a Karl Storz or Olympus resectoscope of 26 Fr.

#### Protocol for Confocal Laser Endomicroscopy in the Upper Urinary Tract

The complete ureter and renal pelvis are inspected with WLC and image enhancement modalities (narrow band imaging or Image1S) during standard flexible digital ureterorenoscopy under general anaesthesia to identify regions of interest. Only in case of visually confirmed upper tract tumors during URS, study-related activities will be performed. If regions of interest are identified, the region that is most easily accessible for endoscopic biopsies is selected for CLE imaging. Fluorescein (0.5 mL of 2.5% fluorescein diluted in saline) is administered through the working channel. The Uroflex-B probe is introduced via the working channel of the 8.5 Fr flexible digital ureteroscope (Karl Storz Flex Xc or Olympus V2) and placed into direct contact with the region of interest for immediate CLE imaging. Each region of interest is imaged twice for approximately 1 minute with CLE. After imaging, endoscopic biopsies for the standard diagnostic process are taken from the same location. Depending on the histopathologic diagnosis, the indication for a radical treatment will be determined.

Cellular morphology	Monomorph or pleiomorph
Definition of cell borders	Distinct or indistinct
Vasculature	Capillary network, fibrovascular stalk, or large vessels

**Figure 2 figure2:**
[figure not shown]
A schematic overview of the data analysis plan. CLE: confocal laser endomicroscopy; PA: histopathology.

### Safety

The investigators will monitor patient safety. They can withdraw a patient from the study for medical reasons. In accordance to section 10, subsection 4, of the “Wet Medisch-Wetenschappelijk Onderzoek met Mensen” (medical research involving human subjects act in The Netherlands), the investigators will suspend the study if there is sufficient ground that continuation of the study will jeopardise patient health or safety. The investigators will notify the accredited Institutional Review Board if this is the case. In case of an adverse event or serious adverse event, the responsible authorities will be informed.

### Risks and Benefits

There are no direct benefits for patients participating in these two studies. In the future, however, the results of these studies may be important for patients diagnosed with a tumor in the urinary tract. All patients participating in both studies are scheduled for standard treatment of tumor(s) of the urinary tract; either TURB or URS with endoscopic biopsies. CLE is a minimally invasive imaging technique that can be performed in conjunction with conventional endoscopic treatment. Previous studies of CLE combined with topical administration of fluorescein have proven to be safe [7,24]. Fluorescein is a commonly used fluorescent dye, and its safety is well established for its use in ophthalmological angiography [25]. In patients not at risk for a previously demonstrated allergic reaction, this dye is safe. Patients with a known allergic reaction to fluorescein cannot participate in this study.

## Results

Presently, recruitment of patients is ongoing in both studies. Results and outcomes are expected in 2018.

Summarized raw data will be made available through publication in an international peer-reviewed medical journal.

## Discussion

CLE is an optical imaging technique that may enable real-time optical biopsies. The exploration of tissue specific CLE criteria is essential for the development towards real-time tumor grading of urothelial lesions. Both trials will provide more insight into CLE features of urothelial carcinoma in the bladder and the upper urinary tract and into its diagnostic value.

The design of the bladder protocol aims for topographic matching of CLE images with the resected specimen. The cauterisation marks placed laterally to the region of interest prior to CLE imaging ensures that imaging and resection is done of the exact topographic tissue. Nonetheless, it will be challenging to create an identical histopathological slide of the resected specimen in exactly the same plane as the imaged tissue. We assume that this approach is the closest approximation for topographic matching without interference in the standard clinical histopathologic process.

The study design of the upper urinary tract protocol will lead to a surplus of study measurements, considering that only about one-third of the UTUC patients will receive radical surgery as treatment. Since mainly patients with high-grade or high-volume low-grade tumor will qualify for radical treatment, selection bias could be a risk. The data acquired of patients who are not suitable for radical treatment enables secondary analysis for the comparison of CLE images with the histology of endoscopic biopsies of the imaged regions of interest. In the current study design, identical topographic matching of CLE images in the upper urinary tract with the specimen of the RNU is limited by the fact that in general the diagnostic URS with CLE imaging is not performed during the same procedure as the radical resection. However, topographic matching is approximated by tumor mapping during URS (mapping and annotation of location, size, and appearance) for identification of lesions during the histopathologic assessment.

As with all new techniques, a learning curve for the handling and image interpretation may be expected for CLE. Besides potential intraobserver variability, the learning process might also influence the CLE image quality of the first cases. We aim to limit the number of users to a minimum number of experienced endourologists to minimize the potential effect of a learning curve.

Despite these limitations, we expect that the results of these trials will contribute to determining the role of CLE imaging for the diagnosis of bladder cancer and UTUC in clinical practice. In the light of the limitations of cystoscopy and URS, CLE holds the potential to enable real-time tumor grading of urothelial carcinoma.

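### Upper tract accuracy rests on a selectively verified subset (about 25 of about 70 patients), and the biopsy comparison that could help gauge the resulting bias is described only for unoperated patients

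*Protocol article*

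**What the plan says.** Population and Sample Size states that "about one-third of the UTUC patients are treated with radical surgery in our centre", and therefore that "we expect to include 70 consecutive UTUC patients to reach the total number of 25 patients who will undergo radical treatment". The same section says the radical indication is settled only after the diagnostic ureterorenoscopy, so imaging comes first. The expected mix already allows for selection: "Considering the possible selection bias for radical treatment, we expect to include 10 low-grade, 12 high-grade, and 3 CIS lesions".

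The upper tract procedure section adds three facts. Study activities take place only when a tumor is seen. After imaging, "endoscopic biopsies for the standard diagnostic process are taken from the same location". The radical indication then depends on the histopathologic diagnosis.

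Data Analysis applies one method to both studies: concordance, sensitivity and specificity against histopathology, which for the upper tract is the RNU/SU specimen, with CIS counted as high-grade. The Discussion says the design "will lead to a surplus of study measurements" and that, since "mainly patients with high-grade or high-volume low-grade tumor will qualify for radical treatment, selection bias could be a risk". It offers the patients not suitable for radical treatment for a secondary comparison of CLE with biopsy histology.

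Table 1 gives the upper tract population as "25 patients with UTUC that will undergo a RNU or SU after diagnostic URS with CLE imaging". The Abstract (Methods) states: "In the upper urinary tract study, CLE will be performed in 25 patients during ureterorenoscopy".

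**The concern.** In the bladder study, the imaged regions are resected, so imaged lesions receive the reference standard. In the upper tract only about a third of patients do, and which third depends on biopsy result and tumor volume. The same crude accuracy calculation is nevertheless planned for both.

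Selection on true grade alone would not distort sensitivity or specificity. The Introduction, however, reports that biopsy grade agrees with resection grade in 69-90% of cases, so a decision driven by biopsy is not driven by true grade alone. Biopsy and CLE sample the same site, and both judge cell organization and morphology. It is plausible, though not shown, that a low-grade tumor over-called on biopsy is also more likely to look high-grade on CLE. If so, such tumors are over-represented among the verified. Apparent specificity for low-grade then falls and apparent sensitivity for high-grade rises. Low-grade is the class for which the Introduction says endoscopic treatment is reserved.

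The plan names the selection risk but describes no adjustment. It also describes the biopsy comparison only for patients without a resection specimen. The operated patients have both a same-site biopsy and a specimen, and they are the link between the two references.

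**Working it through.** **The plan's own figure.** Required inclusions = 25 / fraction operated. At exactly one-third this is 75; at 35% it is 71.4, so 72; at 25/70 = 35.7% it is 70. The stated 70 fits a loose reading of one-third. The expected mix adds up: 10 + 12 + 3 = 25, of which 15 (60%) are high-grade or CIS.

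**Selective verification.** 25/70 = 36% are verified and 45/70 = 64% are not. The figure of 70 is approximate as a count of imaged patients, because imaging needs a visible tumor. The grade mix of all 70 is not given. If low-grade made up 50% to 70% of them, 10/35 to 10/49 (29% to 20%) of low-grade and 15/35 to 15/21 (43% to 71%) of high-grade/CIS patients would be verified.

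**When bias arises.** Reduce the table to high-grade (with CIS) versus low-grade. Let r be the verification probability when CLE reads high, divided by that when CLE reads low, within the same true grade. Then

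- apparent sensitivity = Se·r / (Se·r + 1 − Se)
- apparent specificity = Sp / (Sp + (1 − Sp)·r)

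With true Se = Sp = 0.80 (assumed):

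| r (assumed) | Apparent sensitivity | Apparent specificity |
|---|---|---|
| 1 | 0.80 | 0.80 |
| 1.25 | 0.83 | 0.76 |
| 1.5 | 0.86 | 0.73 |
| 2 | 0.89 | 0.67 |

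The documents give no value of r.

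**One illustration matched to the plan's counts.** Assume 60% of 70 are low-grade (42 low, 28 high). Assume biopsy reads high in 15% of low-grade (6.3 of 42) and in 75% of high-grade (21 of 28). Overall biopsy agreement is then (35.7 + 21)/70 = 81%, and (5.84 + 13.85)/25 = 79% among the verified, both inside 69-90%. Choose surgery rates so that 10 low-grade and 15 high-grade are verified:

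- 6.3a + 35.7b = 10 and 21a + 7b = 15, giving a = 0.660 (biopsy-high) and b = 0.164 (biopsy-low).

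Assume CLE reads high in 50% (biopsy-high) or 15% (biopsy-low) of low-grade, and in 90% or 50% of high-grade.

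- Specificity, all low-grade: (6.3×0.50 + 35.7×0.85)/42 = 0.80. Verified: (4.16×0.50 + 5.84×0.85)/10 = 0.70.
- Sensitivity, all high-grade: (21×0.90 + 7×0.50)/28 = 0.80. Verified: (13.85×0.90 + 1.15×0.50)/15 = 0.87.

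If the two CLE rates within each grade are set equal, both biases vanish.

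**How well an adjustment could do.** In the same illustration, 7×0.164 = 1.15 verified patients represent the 7 biopsy-low, high-grade patients, a weight of about 6 each. Adjusted sensitivity would turn on roughly one patient.

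**The case against.** The strongest reply is that verification follows biopsy histology, not CLE, and the documents show no correlation between the two within true grade; the illustration supplies it. It also leaves out the high-volume low-grade route that the Discussion names, for which the direction of any bias is unknown. All of this stands: a risk has been shown, not an established bias or a size.

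Accuracy is also a secondary, preliminary aim in an exploratory study. With 10 low-grade lesions, a move from 80% to 70% is one patient, and the exact 95% interval for 8/10 is already 44% to 97%. The authors disclose the selection and allow for it in the expected mix. This lowers the weight of the point. It does not explain why the biopsy comparison should leave out the operated patients.

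A reader might infer more from Table 1's population of 25 and the word surplus: that feasibility, adverse events, image quality and observer agreement are confined to the 25, so that 64% of those data are lost. The documents do not support that. The Abstract has all CLE images read by three observers, the 30-day adverse-event follow-up in Study Design is not tied to later surgery, and the Discussion keeps the unoperated patients' data for secondary use. No passage limits these outcomes to the 25.

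**Conclusion.** The point holds as a risk with an inexpensive remedy. Verification by RNU/SU is selective, at about 25 of about 70, and is driven by biopsy histology and tumor volume. The planned crude sensitivity and specificity may therefore be biased. The size depends entirely on how strongly biopsy grade or volume tracks the CLE reading within true grade, and nothing in the documents fixes that. The shift from 80%/80% to 70% specificity and 87% sensitivity is an illustration under the listed assumptions, not an estimate for this trial. To say that the accuracy results will be biased would go beyond the documents.

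The abstract's count also needs correcting. Its sentence goes on to describe the 25 as patients who then have radical treatment, but it gives 25 as the number in whom CLE is performed. Population and Sample Size expects about 70 inclusions, with imaging done before anyone knows who the 25 will be.

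**What to change.** 1. Tabulate CLE diagnosis against same-site biopsy for all imaged patients, operated or not, and keep CLE against RNU/SU in the operated. Showing the biopsy table separately for operated and unoperated patients lets a reader see whether CLE behaves differently in the two groups.
2. Beside the crude estimate, report a verification-adjusted one (Begg-Greenes, or inverse-probability weighting on biopsy grade and tumor size). Label it an exploratory sensitivity analysis, and state that it assumes these variables capture selection for surgery and that it will be imprecise because very few biopsy-low, high-grade patients are verified.
3. Reword the Abstract, and for consistency the population row of Table 1, to say that about 70 patients are included, with CLE performed where a tumor is seen, in order to obtain 25 with RNU/SU.

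The biopsies are part of the standard process, and lesion size is already mapped at ureterorenoscopy according to the Discussion, so no new data are needed. The cost is three-observer reading of the recordings from up to about 45 further patients, which the plan's own secondary analysis already implies, and wide adjusted intervals.
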